#### Secondary objectives

• Determine the acceptability of the intervention based on participant’s engagement.• Seek to understand patients’ perceptions of the barriers and facilitators to face-to-face exercise-based rehabilitation in people with Long Covid.• Explore the effectiveness of a face-to-face rehabilitation programme on other symptoms commonly associated with Long Covid to include fatigue, breathlessness, reduced physical activity, health-related quality of life (HRQoL), anxiety, depression, and pain.• Use a healthcare inequalities lens to explore which demographic groups may be under-represented within Long Covid rehabilitation, with the qualitative work providing further evidence as to why this may be the case.

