### Outcomes {12}

A comprehensive, individualised face-to-face assessment will be conducted for all participants, to include demographics of protected characteristics (to inform the secondary analysis of healthcare inequalities), social history (to include employment status, smoking history), history of presenting complaint (Long Covid history), and comorbidities. Participants’ home postcodes will be indexed to the indices of multiple deprivation (IMD) to inform socioeconomic status. All outcome measures will be performed before and after the 6-week intervention phase. The core outcome set for Long Covid [31] developed through international consensus was consulted to inform which outcome measures were selected for use in this study.

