#### Primary outcome

Maximal exercise capacity was measured by absolute change in ISWT distance (in metres) 6 weeks after baseline (±2 weeks). The ISWT will be performed in line with technical standards [32]. In brief, the test is an externally paced, incremental test that requires the patient to walk around a 10-m (m) course at a target speed dictated by audio bleeps. As a maximal, progressive test, the walking speed starts slowly but increases each minute, with the test terminated when the patient is no longer able to keep up with audio cues or by the assessor if the required speed is not attained. The test will be performed twice pre-intervention for familiarisation, with the highest distance achieved used for exercise prescription (ESWT speed). The test will be repeated once after the intervention (Table 1).

**Table 1 Tab1:** Secondary outcome measures

Acceptability	Physical Measures	Questionnaires
Quantitative measure of completion in the intervention group	Short physical performance battery (SPPB) [33]	Generic HRQoL: EQ-5D-5L [34]
Qualitative evidence via focus groups and semi-structured interviews	Physical activity monitoring: ActiGraph accelerometer device [35]	Fatigue: Functional Assessment of Chronic Illness Therapy Fatigue Scale (FACIT-Fatigue) [36]
	Maximum isometric quadriceps strength (kg) [37]	Depression: Patient Health Questionnaire (PHQ9) [38]
	Endurance Shuttle Walk Test (ESWT) (seconds) [39]	Anxiety: Generalised Anxiety Disorder 7-item scale (GAD7) [40]
		Breathlessness: MRC Dyspnoea scale [41]
		Covid-specific HRQoL: Modified C19-YRS [42]
		Cognitive Function: Montreal Cognitive Assessment (MoCA) [43]
		Post Exertional Malaise: DePaul Symptom Questionnaire Short Form (DSQ-SF) [25]

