### Statistical analysis {20a, 20b and 20c}

The analysis will compare the intervention group to the usual care group. Changes in the primary outcome (ISWT distance) will be compared between the groups using a paired *t*-test (or nonparametric equivalent if the data is not normally distributed). Two sensitivity analyses will be conducted for the primary outcome: (1) Missing data will be imputed using multiple imputation allowing for a full ITT analysis and (2) a per-protocol analysis with those that adhere to the intervention defined if they attended 75% of face-to-face sessions or attended for follow-up appointments.The ISWT will also be analysed using generalised linear mixed models (GLMM); this will allow for in-group adjustments for other variables which may add to the richness of the qualitative data at the point of data mixing.

Secondary outcomes are not powered. All analysis of the primary and secondary outcomes will be performed using R (Version 4.3.1), [48]. Continuous variables will be analysed using the *t*-test or nonparametric equivalent. Categorical variables will be analysed using the chi-squared test or non-parametric equivalent.

Blood biomarkers will be analysed using generalised linear mixed models (GLMM) or similar, with intervention group (control vs face to face), time point (pre vs post), and group × time treated as fixed effects; a random intercept will be included for the participant identifier, and all models will be adjusted for sex and baseline values for each variable.

For the heart rate variability, data will be analysed using robust signal processing approaches by a research associate. Advanced HRV analysis will be performed with the Holter ECGs. Biomarkers of interest include QT variability, signal averaging ECG (fragmented QRS complexes), temporal T-wave morphology variability, and T-wave alternans. These features will be compared and combined to be further correlated with patient-specific characteristics.

GLMMs will be fitted using the lmer function from the lme4 package [49]. Missing data for the primary and secondary outcomes will be imputed using a Bayesian framework. GLMMs will be fitted to outcomes with and without imputation. Imputation was performed using the JointAI library [50].

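### The secondary-outcome rules leave no clear place for the ordered MRC dyspnoea grade; if the chi-squared rule is applied, grade order is lost, and neither rule mentions the baseline grade.

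*Protocol article*

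**What the plan says.** The Statistical analysis section of the protocol article gives two generic rules for secondary outcomes: "Continuous variables will be analysed using the *t*-test or nonparametric equivalent", and "Categorical variables will be analysed using the chi-squared test or non-parametric equivalent". There is no separate rule for ordered categories, and no list says which outcome falls under which rule.

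Table 1, in the Outcomes section, lists "Breathlessness: MRC Dyspnoea scale" among the questionnaires without giving a variable type. The Secondary objectives include exploring the effect on "other symptoms commonly associated with Long Covid to include fatigue, breathlessness, reduced physical activity" and further symptoms.

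Three other statements bear on the point:

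- Outcomes section: "All outcome measures will be performed before and after the 6-week intervention phase".
- Statistical analysis section: "Secondary outcomes are not powered".
- End of the same section: "GLMMs will be fitted to outcomes with and without imputation". It does not say which outcomes are meant. The models are to be fitted with lmer.

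**The concern.** A dyspnoea grade is a short ordered scale, and neither rule plainly fits it. It is a plausible candidate for the categorical rule. Most other Table 1 measures are physical quantities or questionnaire scores, and the one plainly categorical item, completion, is defined for the intervention group only and so cannot be compared between arms.

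Pearson chi-squared gives the same result however the grade columns are shuffled, so a consistent shift towards better grades earns no credit for being consistent. The clause allowing a non-parametric equivalent does not settle the matter. Chi-squared is already nonparametric, and its usual small-sample substitute, Fisher's exact test, also ignores order.

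The baseline grade is a separate issue. It is measured in everyone, but neither rule mentions it. The only models for which adjustment for baseline values is written out are those for the blood biomarkers.

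At stake is the precision of the breathlessness result in a trial with about 46 evaluable people, and a choice of test left open between methods of quite different power.

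**Working it through.** **Figures in the plan.** The article gives no power figure for breathlessness, so there is none to reproduce. From the Sample size section I take 23 evaluable per arm (46 in total) and 56 recruited (46 × 1.2 = 55.2, stated as 56), which is 28 per arm. The 23 per arm does not follow from the stated 50 m and SD of 17 m: an exact two-sample t-test at 90% power and two-sided 0.05 needs 4 per group. That is a separate matter. Here 23 is used only as the planned number.

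**Assumptions not in the documents.** Five ordered grades; a latent normal variable cut into grades; three grade distributions (10/25/30/25/10%, 15/40/25/15/5%, 2/45/40/11/2%); baseline to follow-up correlation of 0.5 or 0.7; latent treatment shifts of 0.4 to 1.0 SD; two-sided 0.05. There were 4,000 simulated trials per scenario.

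**Tests compared, all on follow-up grade.**

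- Chi-squared: X² = Σ(O − E)²/E on the 2 × 5 table, with 4 df when all five grades occur.
- Rank-sum: midranks compared between arms, with tie-corrected variance.
- Rank ANCOVA: rank of follow-up grade regressed on arm and rank of baseline grade, with 2 × 23 − 3 = 43 residual df.

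**Power at 23 per arm** (range over the three distributions and both correlations):

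| Shift | Chi-squared | Rank-sum | Rank ANCOVA | Chi-squared ÷ rank-sum |
|---|---|---|---|---|
| 0.4 SD | 9–13% | 21–25% | 25–36% | 0.43–0.53 |
| 0.6 SD | 19–25% | 42–49% | 49–68% | 0.46–0.54 |
| 0.8 SD | 36–45% | 64–71% | 70–89% | 0.56–0.63 |
| 1.0 SD | 57–66% | 83–88% | 88–98% | 0.69–0.76 |

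Against rank ANCOVA, the chi-squared ratio is 0.30–0.44 at 0.4 to 0.6 SD, 0.46–0.56 at 0.8 SD and 0.61–0.71 at 1.0 SD.

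**A second model.** Proportional odds with control grades of 10/30/30/20/10%, 23 per arm and 5,000 trials per odds ratio gives, for chi-squared against rank-sum:

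- odds ratio 2.5: 19.7% against 40.1% (ratio 0.49);
- odds ratio 3: 28.2% against 51.3% (0.55);
- odds ratio 4: 45.5% against 70.8% (0.64).

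**If nobody is lost (28 per arm).** In the latent model the ratio of chi-squared to rank-sum power runs from 0.44 to 0.83.

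**If only two grades occur.** At 23 per arm, chi-squared and rank-sum have equal power (ratio 1.0), and chi-squared has 0.82–0.97 times the power of rank ANCOVA.

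**Small cells.** With five grades in use the mean expected count per cell is 46/10 = 4.6, so at least one is always below 5. Even so, the false-positive rate of chi-squared was not inflated: 2.6–4.7% in the five-grade latent scenarios at 23 per arm, and 3.9% in the proportional-odds model.

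**The case against.** A reader might infer that the plan tests breathlessness by chi-squared, ignores baseline and so halves the power. The documents do not support that as a flat statement, for four reasons.

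1. No section assigns MRC dyspnoea to the categorical rule. It could be handled under the continuous rule, whose nonparametric equivalent for two arms is the rank-sum test. On that reading there is no loss of order.
2. Non-use of baseline is not certain. The mixed-model sentence follows one on imputing primary and secondary outcomes, so it may reach this outcome. The primary outcome is compared on changes, and the same may be intended for secondary outcomes. Neither settles the point: lmer fits a linear model that treats grades as numbers, and in every five-grade scenario with a treatment effect, rank ANCOVA had more power than a rank-sum test on change.
3. Halving is not a property of the plan. It depends on the assumed number of grades, their distribution and the effect size. The loss is near or above half for small and moderate effects, about a quarter to a third against a rank-sum test at 1.0 SD, and nil if two grades occur.
4. Sparse cells did not make chi-squared invalid in the simulations. The cost is power, not false positives.

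It can also be said that assigning a test to each outcome belongs in an analysis plan that is not shown, and that the outcome is exploratory and declared unpowered. That limits the importance of the point. It does not remove it, because the article does state a two-way rule, and that rule has no clear place for an ordered grade.

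**Conclusion.** The point holds in conditional form. The plan does not say which of its two rules governs MRC dyspnoea. If it is the categorical rule, order is discarded and power is roughly 0.4 to 0.75 times that of a rank-sum test at 23 per arm, given five grades spread as assumed. Under either rule as written, the baseline grade is unused unless the mixed-model sentence is meant to include this outcome. Compared with an unadjusted rank-sum test, adding baseline raised simulated power from 64–71% to 70–89% at a shift of 0.8 SD.

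The consequence is a less precise result on one exploratory secondary outcome. Primary inference is untouched. This is an inexpensive improvement, not an error that threatens the trial.

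**What to change.** State which rule applies to each secondary outcome, and add one for ordered outcomes:

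- Compare MRC grade, and any other ordered outcome, between arms with a proportional-odds model on follow-up grade, adjusted for baseline grade. Report the odds ratio with its 95% CI.
- Keep covariates few. With five grades, the model already has four thresholds, the arm effect and at least one baseline term, so at least six parameters for about 46 people.
- Pre-specify one fallback, a baseline-adjusted rank analysis (rank ANCOVA), with a defined trigger such as non-convergence of the model.
- Reserve chi-squared or Fisher's exact test for unordered categories.
- Say whether the mixed-model sentence covers secondary outcomes and, if so, which analysis is the main one.

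The cost is wording only; no extra data or participants are needed. The small downside is reliance on the proportional-odds assumption. The simulations tested rank ANCOVA, not the proportional-odds model itself, so the adjusted gains shown above are a guide to the size of the benefit and not an exact figure for that model.

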#### Additional exploratory outcome measures

These will be optional outcome measures for patients, which they can opt into via the consent form. These exploratory measures have been included to build on the insights gained from prior research.

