##### Immune Markers {33}

Blood will be collected at baseline and at 6 weeks to assess markers of immune ageing and immune-mediated inflammation including (but not limited to) T-cell surface and intracellular phenotype analysis (with or without stimulation) and circulating biomarkers such as antibodies, cytokines, or other circulating proteins. A total of 50 ml (2 ½ tablespoons) venous blood samples will be taken from the arm by a trained member of the research team at the baseline and 6-week assessment visits. Blood samples will be divided into aliquots. Plasma, serum, and peripheral blood mononuclear cells will be separated. A whole blood sample will also be sent for FBC analysis via routine pathology laboratory analysis.

The samples will be stored at −80 °C (plasma and serum) or −150 °C (PBMCs) confidentially in a coded and anonymised form, in accordance with the Human Tissue Act 2004.

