### Sample size {14}

The sample size for the randomised controlled trial is calculated based on the primary outcome of ISWT distance, with a change of 50 m at 90% power, a standard deviation of 17 m, and 0.05 type 1 error. These figures have been previously determined and referenced in the literature as the minimum important difference and variance for the ISWT [10, 45].

The sample size required is based on a power calculation for a two-sample *t*-test. The pwr.t.test function from the pwr package [46], in R, was used to calculate a required sample size of 23 participants per group, 46 participants in total. This has been inflated by 20% to allow for attrition, and, therefore, 56 participants will be recruited.

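### Exploratory blood biomarkers: the baseline value serves as both an outcome row and a covariate, so the group × time standard error will usually be too small

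*Protocol article*

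**What the plan says.** The protocol article's section Statistical analysis {20a, 20b and 20c} sets out one model for every blood biomarker. The intervention group is a fixed effect, along with "time point (pre vs post), and group × time treated as fixed effects". The same sentence continues that "a random intercept will be included for the participant identifier, and all models will be adjusted for sex and baseline values for each variable". On software, the section says that "GLMMs will be fitted using the lmer function from the lme4 package".

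The section Immune Markers {33} gives the sampling times: "Blood will be collected at baseline and at 6 weeks". There is no third sample. Under Additional exploratory outcome measures, the status of these data is plain: "These will be optional outcome measures for patients".

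Nothing in the article leaves the pre row out of the outcome vector or drops the baseline covariate.

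**The concern.** A pre/post mixed model and a baseline-adjusted model are two different ways of using a baseline measurement. In the first, baseline is an outcome and the random intercept carries the within-person correlation. In the second, baseline is a covariate and only the post value is an outcome. The plan specifies both at once. With two samples per person, the covariate predicts the pre row from itself and absorbs the between-person variation that the random intercept is there to capture.

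What is at stake is the calibration of confidence intervals and p-values for the biomarkers, and some lost precision. Because sampling is optional within a small trial, neither is trivial for those outcomes. The main trial result is not at stake.

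**Working it through.** The plan gives no figure for this model, so there is none to reproduce. The check is algebra followed by simulation.

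**Inputs.** From the protocol: two rows per person, random intercept, sex and baseline as covariates, lmer (Gaussian, intercept variance not below 0, one residual variance), 1:1 allocation, at most 56 people ("56 participants will be recruited"). Assumed, because the protocol does not give them: the pre-post correlation ρ, the pre and post variances, and a two-sided 5% level for the biomarkers.

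**Step 1: residuals.** Let B be the centred baseline with variance s0², b the slope of post on baseline, and se² the residual variance of post given baseline. One coefficient must fit the pre row (slope 1) and the post row (slope b), so it settles at (1+b)/2. The residuals are then:
- pre: +(1−b)/2 × B
- post: −(1−b)/2 × B + error

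Their covariance is −(1−b)²s0²/4, which is never positive. A random intercept can represent only non-negative covariance, so its estimated variance tends to the boundary at 0.

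**Step 2: variance of group × time at that boundary, with m per arm.**
- Model: [(1−b)²s0² + 2se²]/m
- True: [2(1−b)²s0² + 2se²]/m

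With equal unit variances, b = ρ and se² = 1−ρ². These become (1−ρ)(3+ρ)/m and 4(1−ρ)/m, so the SE ratio is √((3+ρ)/4). Large-sample type I error is 2[1−Φ(1.96 × ratio)].

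**Step 3: numbers.** The simulation used REML with the intercept variance free, 56 people, complete data and 1,500 null runs per case.

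| ρ | SE ratio, formula | Type I, formula | Fits at zero | Mean SE with / without baseline covariate | Simulated type I |
|---|---|---|---|---|---|
| 0.3 | √0.825 = 0.908 | 0.075 | 100% | 0.286/0.314 = 0.911 | 0.061 |
| 0.5 | √0.875 = 0.935 | 0.067 | 99.7% | 0.249/0.266 = 0.936 | 0.072 |
| 0.7 | √0.925 = 0.962 | 0.059 | 96.9% | 0.199/0.206 = 0.966 | 0.054 |
| 0.9 | √0.975 = 0.987 | 0.053 | 74.4% | 0.118/0.119 = 0.992 | 0.045 |

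The estimates with and without the covariate had the same empirical SD in every row (for example 0.269 at ρ = 0.5). The fifth column therefore isolates the SE effect, and it agrees with the formula. The simulated type I errors are noisier, with a Monte Carlo standard error of about √(0.05 × 0.95/1500) = 0.006. With 28 people and ρ = 0.5, 95.3% of fits were at zero and type I error was 0.069.

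**Step 4: departures from the simple case.**
- Missing post samples at 20%, the inflation used in the sample size ("This has been inflated by 20% to allow for attrition"): mean SE over empirical SD was 0.852 at ρ = 0.5 and 0.845 at ρ = 0.7, with type I error 0.083 and 0.099.
- Post SD 0.6 times pre SD, ρ = 0.5: b = 0.3 and se² = 0.36 × 0.75 = 0.27. The SE ratio is √[(0.245+0.27)/(0.49+0.27)] = 0.823. Simulated: 0.813, type I error 0.107.
- Post SD 1.5 times pre SD, ρ = 0.5: b = 0.75 and se² = 2.25 × 0.75 = 1.6875. The SE ratio is √[(0.03125+1.6875)/(0.0625+1.6875)] = 0.991. Simulated type I error 0.046, with 69.7% of fits at zero.

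**Step 5: precision.** Variance of ANCOVA on the post value is 2(1−ρ²)/m, against 4(1−ρ)/m for the difference in mean change. The ratio is (1+ρ)/2, that is 0.65, 0.75 and 0.85 at ρ = 0.3, 0.5 and 0.7. The simulation at ρ = 0.5 gave (0.234/0.269)² = 0.757.

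**Step 6: the alternatives.** Across all the 56-person cases, type I error was 0.043 to 0.061 with the baseline covariate dropped, and 0.041 to 0.060 with ANCOVA.

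**The case against.** The strongest reply has four parts.

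- **These are the lowest-tier outcomes.** They are optional and exploratory, and the "0.05 type 1 error" in the protocol belongs to the ISWT sample size. This stands and limits how much the fault can matter. It does not make a miscalibrated interval acceptable.
- **With complete data the estimate is unbiased.** This also stands. The fault lies in the standard error and in precision that is not gained.
- **The wording allows a similar method, and lmer warns of singular fits.** The statistician could change the model without breaching the protocol. That latitude covers the model family and does not remove the double use of baseline. Switching model after a warning would be a data-dependent choice, possibly differing by marker.
- **The size is assumed.** True: the protocol gives no correlation or variance for any marker, and over part of the plausible range the error is negligible.

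Two stronger readings are tempting and are not supported. A reader might infer that the model always forces the intercept variance to zero, so that every marker's p-value is anti-conservative. It does not. At ρ = 0.9 about a quarter of fits stayed off the boundary. At ρ = 0.8 with post SD 1.2 times pre SD (slope 0.96), a separate simulation with 20 per arm had only about 40% of fits at zero and a calibrated standard error (ratio 0.98 to 1.00). A reader might also take the reference to all models as covering the mixed model planned for the ISWT. Those words sit in the biomarker sentence, and the article lists no covariates for the ISWT model, so nothing can be concluded about it.

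**Conclusion.** The biomarker model is wrong as written, for the optional exploratory blood markers only. Two sampling times make the pre row and the covariate identical. At low to moderate correlation the random intercept then usually collapses and the rows are treated as independent. With equal variances and complete data, the SE is about 9%, 6% and 4% too small at assumed correlations of 0.3, 0.5 and 0.7, with a type I error of roughly 6 to 7.5%. It is about 15% too small with a fifth of post samples missing, and nearly 20% too small if post SD falls to 0.6 of pre SD. It is essentially right when the slope of post on baseline is near 1. The primary ISWT comparison does not use this model and is untouched. This is worth correcting, but it does not threaten the trial's main conclusion.

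**What to change.** Enter baseline on one side of the model only, and say which. Either option is sound:

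- **ANCOVA:** regress the 6-week biomarker value on arm, baseline value and sex, with no pre rows and no random intercept. This is the more efficient choice at low to moderate correlation.
- **Pre/post mixed model:** keep group, time, group × time, sex and the random intercept, and drop the baseline covariate. Constraining the arm means to be equal at baseline is an optional refinement.

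The choice should be fixed before unblinded biomarker data are seen and applied to all markers. It costs one sentence in the analysis section, with no change to data collection, sample size or trial conduct.
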